### Endpoints

The primary endpoints of the study are TIMI flow grade, corrected TIMI frame count, and myocardial blush grade, to document the patency of the culprit vessel. All of these are measured during coronary angiography pre-PCI.

Secondary endpoints are ST resolution based on a 12-lead ECG registration during ultrasound, PCI and post-PCI, infarct size derived from measurement of the marker enzymes, and wall motion abnormalities (WMA) measured with 2D-echo and contrast enhanced MRI.

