**Methods/design -:**

In our multicenter, randomized, placebo controlled clinical trial we will include patients between 18 and 80 years of age with their first ST-elevation myocardial infarction based on a proximal lesion of the infarct-related artery. After receiving a single bolus alteplase 50 mg IV (Actilyse^® ^Boehringer Ingelheim GmbH), a loading dose of aspirin 500 mg, and heparin 5000 IU in the ambulance according to the prehospital thrombolysis protocol, patients, following oral informed consent, are randomized to undergo 15 minutes of pulsatile ultrasound with intravenous administration of ultrasound contrast agent or placebo without ultrasound. Afterwards coronary angiography and, if indicated, percutaneous coronary intervention will take place. A total of 60 patients will be enrolled in approximately 1 year.

The primary endpoints are based on the coronary angiogram and consist of TIMI flow, corrected TIMI frame count, and myocardial blush grade. Follow-up includes 12-lead ECG, 2D-echocardiography, cardiac MRI, and enzyme markers to obtain our secondary endpoints, including the infarct size, wall motion abnormalities, and the global left ventricular function.

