### Statistical analysis

The aim of this pilot study is to investigate whether the combination of ultrasound and microbubbles enhance clot dissolution after pre-treatment of STEMI patients with a loading dose of aspirin 500 mg, heparin 5000 IU, and alteplase single bolus 50 mg.

The reason we use a single bolus alteplase is to avoid serious adverse events. The PACT-trial[26] showed there was no difference in severe complications between the placebo group and the single bolus alteplase group after pre-treatment with aspirin and heparin, but there still was a significant increase in TIMI 3 flow in the alteplase group (33%) compared to placebo (15%). With our study we are aiming for 65% TIMI 3 flow in the group treated with microbubbles. In order to demonstrate this with a power of 80% and an α of 0.05 (two sided) we need a sample size of 29 patients per group. Therefore, we are intending to randomize 60 patients in this pilot study.

Obtained baseline data will be presented as mean ± standard deviation (SD). Differences between the treatment group, with ultrasound and microbubbles, and the control group in baseline data, biomarkers, 2D-echo, and MRI variables will be assessed by unpaired students t-test.

Chi-square analyses will be conducted to observe differences in primary and secondary endpoints between the treatment group and the control group.

All analysis will be performed based on an intention-to-treat principle.

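### Three unranked primary endpoints, one of them sized, and no rule for what counts as a positive primary result

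*Protocol article*

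**What the plan says.** The Endpoints section of the protocol article names three primary endpoints, all read from the angiogram before PCI: "The primary endpoints of the study are TIMI flow grade, corrected TIMI frame count, and myocardial blush grade". The abstract (Methods/design) gives the same list: "The primary endpoints are based on the coronary angiogram and consist of TIMI flow, corrected TIMI frame count, and myocardial blush grade". Neither place orders the three, combines them, or says how many must be positive.

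The Statistical analysis section treats one quantity only when it sets the sample size. It takes 33% TIMI 3 flow from the alteplase arm of a cited trial and continues: "we are aiming for 65% TIMI 3 flow in the group treated with microbubbles". For 80% power at a two-sided alpha of 0.05 it concludes that "we need a sample size of 29 patients per group", and so "we are intending to randomize 60 patients in this pilot study". This is the only alpha in the document, and it is not divided.

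The test is then given for all endpoints together: "Chi-square analyses will be conducted to observe differences in primary and secondary endpoints between the treatment group and the control group".

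**The concern.** The sample size statement and the endpoint list describe different trials. The first has one primary hypothesis, about TIMI 3 flow. The second has three primary endpoints of equal standing. A reader cannot tell from the text what result would make the trial positive.

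This matters in both directions. If one significant endpoint of three is enough, the 5% error rate in the sample size statement does not apply to the trial's conclusion. If all three are needed, the 80% power does not apply, because nothing was assumed about frame count or blush grade. With the rule left open, it could also be chosen after the three results are known.

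**Working it through.** **Inputs.** From the protocol article: three primary endpoints (Endpoints; abstract); TIMI 3 flow 33% versus 65%, power 80%, two-sided alpha 0.05, 29 per group, 60 in total and so 30 per group if split equally (Statistical analysis). Assumed: the correlation r between the three test statistics, which the document does not give.

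**1. The plan's own figure.** Pooled two-sided formula, with mean proportion (0.33 + 0.65)/2 = 0.49:

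n = [1.960 × √(2 × 0.49 × 0.51) + 0.842 × √(0.33 × 0.67 + 0.65 × 0.35)]² / 0.32² = 37.1, so 38 per group.

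Other two-sided variants give 35 (unpooled), 37 (arcsine) and 44 (continuity correction). The stated 29 is not reproduced as a two-sided figure. A one-sided 5% test gives 29.1, so 30. Two-sided power is 69% at 29 per group and 71% at 30. This is a separate problem, and the present point does not depend on it. What counts here is that TIMI 3 flow is the only endpoint in the calculation.

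**2. If any one endpoint suffices, each tested at two-sided 5%.** Under independence the chance of at least one false positive is 1 − 0.95³ = 1 − 0.857 = 14.3%. For correlated tests, three equally correlated normal statistics were simulated (2 million draws per value, rejecting if |z| > 1.96):

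| Assumed r | At least one false positive |
|---|---|
| 0 | 14.3% |
| 0.3 | 13.6% |
| 0.5 | 12.5% |
| 0.7 | 11.0% |
| 0.8 | 9.8% |
| 0.9 | 8.3% |
| 0.95 | 7.4% |
| 1 | 5.0% |

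Only near-perfect correlation brings the figure back to 5%.

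**3. If all three must be significant.** The type I error cannot exceed that of any single test, so it is at most 5%. The power likewise cannot exceed the power for TIMI 3 flow alone. As an illustration, suppose each endpoint had the claimed 80% power. Joint power would then be 0.8³ = 51% under independence and would reach 80% only if the three always succeeded or failed together. The document gives no basis for the 80% on frame count or blush grade.

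**4. If alpha were split later.** At 0.05/3 = 0.0167 per endpoint, the power for 33% versus 65% with 30 per group is

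Φ{[0.32 × √30 − 2.394 × √(2 × 0.49 × 0.51)] / √(0.33 × 0.67 + 0.65 × 0.35)} = Φ(0.09) = 54%

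(52% by exact calculation for the Pearson test). Reaching 80% would need 50 per group, or 56 with continuity correction. A later split therefore cannot be reconciled with the stated sample size.

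**The case against.** Four arguments deserve weight.

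- **The inflated error rate is not in the text.** A reader might infer that each endpoint is tested at 5%, that any one success makes the trial positive, and that the error is therefore 14% instead of 5%. The document says none of this. The 0.05 appears once, attached to TIMI 3 flow, and no success rule is given. The 14.3% also needs independent tests, which is implausible for three readings of the same pre-PCI angiogram of the same culprit vessel. This objection stands, so the inflation can only be stated conditionally.
- **It is a pilot.** The article says so repeatedly and looks forward only to further research. That lowers the severity. It does not remove the point, because the Statistical analysis section uses a formal frame of 80% power at a fixed two-sided alpha, and such a frame needs a defined positive result.
- **An analysis plan may deal with it.** The method of adjustment and the order of testing can be left there, and their absence is not the complaint. The choice of primary endpoint is a protocol decision, and this document has made it in two ways that do not match.
- **TIMI 3 flow is a category of TIMI flow grade and so leads in practice.** This is reasonable, and it supports the fix. But no passage says that TIMI 3 flow takes precedence over the other two.

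**Conclusion.** The point holds as a mismatch inside the protocol article: three unranked primary endpoints, one of them sized, and no rule for success. Its consequence depends on the rule that is eventually applied.

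- **Any one endpoint at 5% is enough:** the false-positive chance is about 8% to 12.5% for assumed correlations of 0.9 to 0.5, and at most 14.3% for independent tests. The correlations are assumptions.
- **All three are required:** the error is at most 5%, and the 80% power is unsupported.

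The documents do not support a flat statement that the trial's error rate is 14%, or that it is inflated at all, because both the any-one rule and the 5% level for each endpoint are inferences. Under neither rule, however, do the stated 5% and 80% hold together for the set of three. For a 60-patient pilot this should be corrected, but it is not a fatal flaw.

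**What to change.** By dated amendment, before any unblinded data are seen:

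1. Name TIMI 3 flow (versus TIMI 0–2) on the pre-PCI angiogram as the single primary endpoint, tested at two-sided 5%. It is the endpoint already sized.
2. Make corrected TIMI frame count and myocardial blush grade secondary. Either test them in a pre-stated order only if TIMI 3 flow is significant, or report them as estimates with confidence intervals. Which of the two is used, and in which order, is for the investigators to choose; it needs to be written down.

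**Cost.** There are no extra patients or measurements, and the stated 5% then applies to the trial's conclusion. A positive frame count or blush grade alone could no longer be claimed as the primary result. Since the abstract says that the trial has been launched, this is a change of endpoints and more than an edit of wording: the amendment must be dated and justified, and the registered endpoints updated to match. It does not repair the separate discrepancy in the sample size calculation.

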### Cardiac imaging

The ultrasound equipment used in this protocol is the Ie33 (Philips, Eindhoven, the Netherlands). In combination with a X3-1 probe we make 3D full volume images of the aortic root in the parasternal short axis view to ensure that the proximal parts of the epicardial coronary artery system is encompassed within the target zone.

The mechanical index will be set on 1.18 in order to make the microbubble collapse. The frequency we will use is 1.6 MHz intermittently (5 seconds on, 5 seconds off) to ensure the microbubbles to enter the proximal portion of the occluded coronary artery between the pulses.

During follow-up, a 2D echo will be performed to obtain information about wall motion abnormalities, left ventricle volumes, and ejection fraction.

The standard emergency coronary angiogram will be performed to assess the patency of the culprit lesion, the TIMI flow, the corrected TIMI frame count, and the myocardial blush grade. To obtain the myocardial blush grade the angiographic runs will be prolonged until the venous phase of the contrast passage is seen[24]. The frame rate will be set on 12,5 frames/sec. To calculate the corrected TIMI frame count the score will be adjusted for the used frame rate[25]. If necessary, a PCI will be carried out.

Patients are studied on a clinical 1.5 Tesla MRI scanner within 2 to 9 days after primary PCI, and for 4-month follow-up. ECG-gated cine SSFP (Steady State Free Precession) MR images are obtained during repeated breath-holds in the three standard long axis views (four-, three- and two-chamber view). Additional short axis slices are acquired covering the entire left ventricle, to examine regional and global left ventricular function.

After that i.v. injection of Gd-DTPA first-pass perfusion imaging is performed with a saturation-recovery gradient-echo pulse sequence. Delayed contrast-enhanced images are acquired 10 minutes post-contrast with an inversion-recovery gradient-echo pulse sequence to identify the location and extent of myocardial infarction. The data are obtained with slice locations identical to the functional images.

### Follow-up

Follow-up examination will exist from 12-lead ECG registration, 2D-echocardiography, contrast enhanced MRI, and biomarkers of myocardial infarction (CK-MB). All serving to achieve the secondary endpoints of this study.

MRI and 2D-echocardiography will be used to assess the global and regional wall motion, left ventricular function, and left ventricular ejection fraction. 12-lead ECG registration will be used to observe the ST-segment resolution and markers to compare infarct size of both groups.

### Statistical analysis

The aim of this pilot study is to investigate whether the combination of ultrasound and microbubbles enhance clot dissolution after pre-treatment of STEMI patients with a loading dose of aspirin 500 mg, heparin 5000 IU, and alteplase single bolus 50 mg.

The reason we use a single bolus alteplase is to avoid serious adverse events. The PACT-trial[26] showed there was no difference in severe complications between the placebo group and the single bolus alteplase group after pre-treatment with aspirin and heparin, but there still was a significant increase in TIMI 3 flow in the alteplase group (33%) compared to placebo (15%). With our study we are aiming for 65% TIMI 3 flow in the group treated with microbubbles. In order to demonstrate this with a power of 80% and an α of 0.05 (two sided) we need a sample size of 29 patients per group. Therefore, we are intending to randomize 60 patients in this pilot study.

Obtained baseline data will be presented as mean ± standard deviation (SD). Differences between the treatment group, with ultrasound and microbubbles, and the control group in baseline data, biomarkers, 2D-echo, and MRI variables will be assessed by unpaired students t-test.

Chi-square analyses will be conducted to observe differences in primary and secondary endpoints between the treatment group and the control group.

All analysis will be performed based on an intention-to-treat principle.

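### 29 patients per group does not give 80% power at two-sided 5% for 33% versus 65%: about 38 are needed, and the planned 60 patients give about 70%

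*Protocol article*

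**What the plan says.** The sample-size reasoning is in the Statistical analysis section of the protocol article. It cites an earlier trial in which TIMI 3 flow was 33% after single-bolus alteplase and 15% on placebo. For the present trial it says "we are aiming for 65% TIMI 3 flow in the group treated with microbubbles". It then states that for "a power of 80% and an α of 0.05 (two sided) we need a sample size of 29 patients per group", and draws the total from this: "we are intending to randomize 60 patients in this pilot study". The Abstract (Methods/design) repeats the total: "A total of 60 patients will be enrolled in approximately 1 year".

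The same section names chi-square analyses for the primary endpoints, of which TIMI flow grade is one. Every patient receives the alteplase bolus before the study treatment (Abstract, Methods/design; Study design), so the 33% describes the background treatment of the control arm.

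**The concern.** A difference of 32 percentage points around a mean rate of 49% normally needs more than 29 per group at two-sided 5% and 80% power. The printed figure looked like the result of a one-sided calculation labelled two-sided.

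This sentence is the only justification given for 60 patients, and it promises 80% power. If the true power is lower, a non-significant result carries less information than readers are told, and may be taken as stronger evidence against the treatment than it is.

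**Working it through.** **Inputs** (all from Statistical analysis)

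- Control rate p1 = 0.33. The article does not label it as the control assumption, but it is the only rate given for single-bolus alteplase, which both arms receive.
- Treated rate p2 = 0.65, so the difference is d = 0.32 and the mean rate is 0.49.
- Power 80%, z = 0.8416.
- Alpha 0.05: z = 1.96 two-sided, 1.645 one-sided.
- Equal groups, chi-square test.

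Two quantities recur: √(2 × 0.49 × 0.51) = 0.7070, and √(0.33 × 0.67 + 0.65 × 0.35) = √0.4486 = 0.6698.

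**1. Trying to reproduce 29**

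The chi-square (pooled under the null) formula is n = [zα × 0.7070 + zβ × 0.6698]² / d².

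- Two-sided: (1.96 × 0.7070 + 0.8416 × 0.6698)² / 0.1024 = 1.949² / 0.1024 = 37.1, so **38 per group**.
- One-sided: (1.645 × 0.7070 + 0.8416 × 0.6698)² / 0.1024 = 1.727² / 0.1024 = **29.1**, which matches the printed figure when rounded to the nearest whole number.

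**2. Other formulas, same rates and power**

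| Formula | Two-sided 5% | One-sided 5% |
|---|---|---|
| Chi-square, pooled | 37.1 → 38 | 29.1 |
| Unpooled variance | 34.4 → 35 | 27.1 |
| Arcsine | 37.0 → 37 | 29.1 |
| Continuity-corrected | 43.1 → 44 | 36 |

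No two-sided formula comes near 29; the most lenient asks for 35. Using the 15% placebo rate as control gives 14 per group two-sided, so that does not explain 29 either.

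**3. Power at the stated and planned numbers, two-sided 5%**

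Normal approximation: power = Φ[(d√n − 1.96 × 0.7070) / 0.6698].

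- n = 29: (1.723 − 1.386) / 0.6698 = 0.504, power 69.3%.
- n = 30: (1.753 − 1.386) / 0.6698 = 0.548, power 70.8%.

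| Method | 29 per group | 30 per group |
|---|---|---|
| Normal approximation, pooled | 69.3% | 70.8% |
| Pearson chi-square, exact enumeration | 69.3% | 72.0% |
| Arcsine | 69.9% | 71.4% |
| Normal approximation, unpooled | 73.0% | 74.4% |
| Yates-corrected or Fisher | 59.2% | 62.3% |

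The last row applies only if the chi-square test is run with a continuity correction or replaced by Fisher's test. The article mentions neither.

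**4. What 30 per group can detect with 80% power**

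Solving for p2 with p1 = 0.33 gives 68.5% by the normal approximation and 68.1% by exact enumeration of the Pearson test.

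**5. Precision with 30 per group**

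At the planned rates, the expected half-width of the 95% confidence interval for the difference is 1.96 × √(0.4486 / 30) = 0.24, or 24 percentage points.

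**The case against.** - **The one-sided explanation is an inference.** This stands. The article does not say a one-sided value was used, and strict rounding up of 29.1 gives 30. Other routes also land close: a 29% control rate against 65% gives 28.96 two-sided, and the stated rates at 70% power give 29.5. None of these uses the figures printed, however. Whatever the cause, 29 is wrong for the inputs given.
- **33% is not declared as the control assumption.** This is true, and the result is conditional on it. But no other alteplase rate is printed, and the only other rate, 15%, does not reproduce 29.
- **The size of the shortfall depends on the formula.** For the uncorrected test at 30 per group it ranges from 70.8% to 74.4%. All values are below 80%, and the exact calculation for the Pearson test gives 72.0%.
- **This is a pilot, and the error does not bias the estimate or the type I error.** This is also true, and a pilot may accept lower power. But the article does not defend 60 on grounds of feasibility. It derives the number from a formal claim of 80% power.
- **Sixty is more than 58.** The two extra patients add 1.5 points of power (69.3% to 70.8%) and leave the total 16 short of 76.

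**Conclusion.** The sample-size statement is wrong as written. At 33% versus 65%, two-sided 5% and 80% power, 38 patients per group are needed by the formula that corresponds to the planned chi-square test, and 35 to 44 across the standard alternatives; the article states 29. With the planned 30 per group, power is about 70% (70.8% approximate, 72.0% exact), so the type II error is 28% to 29% rather than 20%.

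This rests on a 33% control rate, equal groups, no loss of evaluable angiograms and an uncorrected chi-square test. A continuity correction or missing angiograms would lower the power further. The conclusion that 29 is wrong does not depend on how it arose; a one-sided critical value is the likeliest source.

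**What to change.** Correct the sentence and keep 60 patients. Suggested wording:

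> With 30 patients per group, a two-sided chi-square test at the 5% level has about 70% power to detect 33% versus 65% TIMI 3 flow, and 80% power to detect 33% versus about 68.5%. About 38 patients per group would be needed for 80% power at 33% versus 65%.

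State explicitly that 33% is the assumed control rate. This costs wording only: no extra patients and no change to the analysis, though the stated power becomes less favourable.

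If the sponsor wants true 80% power at the stated rates, the alternative is about 76 patients (2 × 38), 16 more than planned.

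It would also help to report the difference in TIMI 3 rates with its 95% confidence interval as the main result. With an expected half-width of about 24 points, the interval shows directly how little a non-significant result would exclude. This is advisable, but the correction does not depend on it.

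### Corrected TIMI frame count is a numeric primary endpoint, but the only test named for it is chi-square, with no categories and no stated value for an artery that cannot be counted

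*Protocol article*

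**What the plan says.** The Endpoints section of the protocol article lists the primary endpoints without ranking them: "The primary endpoints of the study are TIMI flow grade, corrected TIMI frame count, and myocardial blush grade". On timing it says: "All of these are measured during coronary angiography pre-PCI".

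The Cardiac imaging section shows that the frame count is a numeric score. "The frame rate will be set on 12,5 frames/sec", and "To calculate the corrected TIMI frame count the score will be adjusted for the used frame rate". No cut-point or classes for it appear anywhere in the article. The same section describes microbubbles that are meant to "enter the proximal portion of the occluded coronary artery between the pulses", and the inclusion criteria under Study design are chosen to select a blocked proximal artery.

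The Statistical analysis section names two tests. The t-test covers baseline data and "biomarkers, 2D-echo, and MRI variables will be assessed by unpaired students t-test". For the endpoints it says: "Chi-square analyses will be conducted to observe differences in primary and secondary endpoints between the treatment group and the control group". It closes with: "All analysis will be performed based on an intention-to-treat principle".

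**The concern.** Chi-square compares frequencies across categories. The frame count has none in this plan, and the t-test list does not include it, so the one test that the plan attaches to this primary endpoint does not fit its scale. Used on the counts as they stand, the test spreads at most 60 patients over many distinct values and ignores their order.

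The timing adds a second difficulty. A frame count presumably needs contrast to travel down the vessel, so an artery with no distal flow has no natural count. That is an inference from the nature of the measure; the article does not say it. Such arteries would lie among those below TIMI 3. On the plan's own targets that group is 100% - 33% = 67% of controls and 100% - 65% = 35% of treated patients. If treatment works as hoped, uncountable arteries should therefore be more common in the control arm. Leaving them out would compare only arteries that had opened, a subgroup formed by the outcome.

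At stake is whether one of the three primary endpoints has a workable analysis fixed before the data are seen.

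**Working it through.** **The plan's own figure.** The article gives no power or sample size for the frame count. Its only calculation is for TIMI 3 flow: 33% versus 65%, two-sided alpha 0.05, 80% power, 29 per group, 60 randomised. The usual two-proportion formula gives (1.96 × √(2 × 0.49 × 0.51) + 0.84 × √(0.33 × 0.67 + 0.65 × 0.35))² / 0.32² ≈ 37.1, so 38 per arm, and about 71% power at 30 per arm. That discrepancy is a separate matter; here the 71% serves only as a yardstick.

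**Why chi-square on raw counts fails.** Suppose all N counts differ. Each column of the table then holds one patient. A patient in arm 1 contributes n₂/n₁ to the statistic and a patient in arm 2 contributes n₁/n₂. The total is n₁(n₂/n₁) + n₂(n₁/n₂) = N on N - 1 degrees of freedom, whatever the treatment did. For N = 60 the statistic is 60 on 59 degrees of freedom, p = 0.44. Ties loosen this result only partly.

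**Simulation with ties.** The document supplies 30 per arm (60 in total) and TIMI 3 rates of 33% and 65%. The following are assumptions:

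- Scenarios A to C: count mean 26 (SD 8) with TIMI 3 flow and 60 (SD 18) in other open arteries.
- Scenario D: TIMI 0/1/2/3 of 35/12/20/33% in controls and 12.5/6.5/16/65% in treated patients; count mean 35 (SD 12) for TIMI 3 and 70 (SD 20) for TIMI 2. TIMI 0-1 is taken as uncountable: 35 + 12 = 47% and 12.5 + 6.5 = 19%.
- Counts fall in steps of 30/12.5 = 2.4, taking 30 frames/s as the reference rate.

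Rejection rate at nominal 0.05:

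| Analysis | A: uncountable 25% control, 15% treated | B: 40%, 20% | C: 50%, 25% | D: 47%, 19% |
|---|---|---|---|---|
| Chi-square on raw counts, uncountable dropped | 1.5% | 1.3% | 1.1% | 0.4% |
| Chi-square on raw counts, uncountable as a category | 3.4% | 7.4% | 11.0% | 11% |
| Rank test, open arteries only | 43% | 27% | 16% | 14% |
| t-test, open arteries only | 46% | 32% | 22% | 16% |
| Rank test, uncountable at worst rank | 50% | 59% | 60% | 66% |
| Chi-square, cut at 40, occlusion as failure | 58% | 63% | 66% | 37% |

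In scenario D a cut at 50 instead of 40 gives 60%. Neither cut comes from the document.

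In A to C the open arteries take about 18 to 23 distinct values. In B, for example, 0.60 × 30 + 0.80 × 30 = 42 open arteries over about 20.4 values give 42 / (2 × 20.4) ≈ 1.0 expected patient per cell.

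Over all runs under these and similar assumptions, the rounded ranges are:

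- 0.4-2% for chi-square on raw counts with uncountable arteries dropped;
- 3-13% for chi-square with them as a category;
- 12-46% for a rank test or t-test in open arteries only;
- 50-68% for the worst-rank test;
- 36-69% for chi-square on a cut-point.

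**The case against.** Chi-square needs categories, so the natural reading is that the frame count would be grouped before testing; nothing says that it will be run on ungrouped values. With a sensible cut and occlusion counted as failure, chi-square does about as well as the worst-rank test in most scenarios. This stands: chi-square is not inherently uninformative here. It does not remove the point, because the article gives no grouping, the result depends on the cut (37% against 60% in scenario D), and a cut chosen after seeing the data would be open to selection.

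A reader might also infer that the plan drops patients with occluded arteries. The documents do not support that. No section prescribes an exclusion, and the Statistical analysis section states intention to treat. The article is silent on the value such an artery receives, and a full protocol or SAP may supply the rule. That part is therefore a clarification to seek, and the low open-artery figures describe a route to avoid, not one that the plan has chosen.

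Finally, this is a pilot whose sample size rests on the TIMI 3 proportion, for which chi-square is suitable. It is also usable, though blind to order, for the TIMI and blush grades. This stands and limits the reach of the defect.

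**Conclusion.** The point holds in limited form. The article does not merely omit a detail: it assigns a test to a numeric primary endpoint that does not fit its scale, and gives no categories that would make it fit. Followed literally, the comparison has about 0.4-2% power, or 3-13% with uncountable arteries as a category, against about 50-68% for a rank test that keeps everyone. The sizes depend on assumed count distributions and occlusion shares. In every scenario tried, chi-square on raw counts did far worse than either remedy.

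Two stronger readings go too far. One is that the trial would give a wrong answer: only this endpoint is affected, and the TIMI 3 comparison is untouched. The other is that the plan commits itself to an open-artery analysis: it does not. This should be fixed, but it does not undermine the trial's main comparison.

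**What to change.** Amend the Statistical analysis section so that corrected TIMI frame count is taken out of the general chi-square sentence and compared by a Wilcoxon rank-sum test on all randomised patients, with arteries that yield no measurable count given the worst rank. Report the probability of a better outcome or a Hodges-Lehmann difference alongside it. Alternatively, keep chi-square but prespecify a cut-point, with occlusion counted as failure. Under either option, state how an uncountable artery is scored, and show open-artery values only as description.

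The cost is analysis wording, with no new data, patients or procedures. The small downside is that a worst-rank result is less directly interpretable in frames; the cut-point version is easier to read, but its power depends on where the cut falls.
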